## Abstract

**Background:**

Potassium depletion is common in hospitalized patients and can cause serious complications such as cardiac arrhythmias. In the intensive care unit (ICU) the majority of patients require potassium suppletion. However, there are no data regarding the optimal control target in critically ill patients. After open-heart surgery, patients have a strongly increased risk of atrial fibrillation or atrial flutter (AFF). In a novel trial design, we examined if in these patients different potassium control-targets within the normal range may have different effects on the incidence of AFF.

**Methods/Design:**

The "computer-driven Glucose and potassium Regulation program in Intensive care Patients with COMparison of PotASSium targets within normokalemic range (GRIP-COMPASS) trial" is a single-center prospective trial in which a total of 1200 patients are assigned to either a potassium control-target of 4.0 mmol/L or 4.5 mmol/L in consecutive alternating blocks of 50 patients each. Potassium levels are regulated by the computer-assisted potassium suppletion algorithm called GRIP-II (Glucose and potassium regulation for Intensive care Patients). Primary endpoint is the in-hospital incidence of AFF after cardiac surgery. Secondary endpoints are: in-hospital AFF in medical patients or patients after non-cardiac surgery, actually achieved potassium levels and their variation, electrolyte and glucose levels, potassium and insulin requirements, cumulative fluid balance, (ICU) length of stay, ICU mortality, hospital mortality and 90-day mortality.

**Discussion:**

The GRIP-COMPASS trial is the first controlled clinical trial to date that compares potassium targets. Other novel methodological elements of the study are that it is performed in ICU patients where both targets are within the normal range and that a computer-assisted potassium suppletion algorithm is used.

**Trial registration:**

NCT 01085071 at ClinicalTrials.gov

## Background

Potassium disorders occur frequently in hospitalized patients [1,2] and it has long been known that extreme potassium values can cause life-threatening complications, especially in critically ill patients [3,4]. However, the effects on outcome of less pronounced differences in the potassium concentration, that occur much more frequently, are not known.

As is the case with most laboratory parameters, plasma potassium values are considered as "normal" when they equal those observed in a healthy reference population. Although desirable levels for some laboratory parameters in critically patients may equal healthy reference levels, for others, such as hemoglobin, albumin or calcium, this is not the case [5-7]. Although potassium is administered to the majority of intensive care unit (ICU) patients, the optimal level in critically ill patients has never been investigated. There are no prospective trials concerning potassium regulation and only a few observational studies and reviews that describe the treatment once severe potassium disorders have developed [3,8,9]. Potassium has recently been involved in the debate on the disparate results of the Leuven [10] and NICE-SUGAR [11] trials that both compared glucose control targets, since the outcome of tight glucose control might be affected by potentially insufficiently controlled potassium levels [12].

Potassium regulation in the critically ill patient can be performed by titrated continuous potassium infusion. To avoid hyper- and hypokalemia, regular plasma potassium measurements and subsequent adjustments of the infusion rate are necessary [13-16]. To achieve two target values within a narrow range an effective potassium regulation protocol is mandatory. For safety and efficiency, computerized protocols appear to be superior over paper protocols [17-19]. In our ICU we have implemented an integrated computer-assisted program for both glucose and potassium regulation that is called GRIP-II (Glucose and potassium Regulation for Intensive care Patients) [20-22]. This program provides a recommendation on the potassium and insulin infusion rates and the time to the next potassium and glucose measurement. These recommendations are mainly based on the current potassium and glucose levels and analysis of their trend over time. In a before-after study comparing GRIP-II potassium control with physician-driven potassium control, potassium control improved with a significantly reduced number of hypokalemic and hyperkalemic events [20]. In the latter study the GRIP-II program aimed for a potassium level in the middle of the normal range of 3.5-5.0 mmol/L, i.e 4.3 mmol/L. However, it is not known what the effects would be when the target would be slightly different, i.e in normal-low or normal-high target range.

Potassium is the main intracellular cation of the body. The intracellular to extracellular potassium ratio affects both the fluid balance and the resting membrane potential. The reference plasma potassium ranges from 3.5 to 5.0 mmol/L. Levels below 3.0 mmol/L or above 6.0 mmol/L can cause serious symptoms of which cardiac arrhythmias are the most frequently observed [4]. After cardiac surgery (especially valvular surgery) postoperative atrial fibrillation is one of the most common complications with a reported incidence of 10-50%. It is associated with adverse outcome and despite new treatment strategies the incidence remains high [23-26]. After a potassium load, the intracellular compartment acts as the primary buffer. A potassium shift from extracellular to intracellular is caused by increased activity of the Na-K-ATPase pump, which can be directly stimulated by an increase in plasma potassium, insulin, catecholamines, aldosterone and alkalosis [27-29]. The most important organs in the homeostasis of potassium are the kidneys as they normally excrete or reabsorb potassium according to the overall potassium balance [30]. There is some evidence that a normal-high plasma potassium level is preferable in several cardiovascular states [31-33]. However, the optimal potassium level in the critically ill patient, who may be especially prone to the adverse effect of potassium derangements, has never been investigated prospectively. A cautious approach towards finding best target levels for potassium seems justified given the problematic discussions over optimal glucose targets in ICU patients [10,12]. A computer-assisted potassium regulation program such as GRIP-II provides the opportunity to perform a clinical trial to safely and efficiently compare two potassium targets within the normal range.

In this prospective phase 4 trial we will compare the effect of two different potassium control-target values that are both within the reference range of 3.5 - 5.0 mmol/L. In the NLP (Normal-Low Potassium) trial arm a normal-low potassium level of 4.0 mmol/L is aimed for, while in the NHP (Normal-High Potassium) trial arm a normal-high potassium level of 4.5 mmol/L is aimed for. We hypothesize that both physiological and pathophysiological differences may exist between the normal-low and the normal-high potassium control targets. In the study all patients are allocated to either the 4.0 or 4.5 mmol/L control target in alternating blocks of patients.

The GRIP-COMPASS trial thus constitutes a novel trial in a number of aspects. It is the first clinical trial to assess the effect of different potassium target levels. Also it is the first trial to compare two control-targets that are both within the reference range in critically ill patients. Furthermore this trial compares two treatment strategies that both are executed by a computer-based potassium suppletion algorithm.

## Methods/Design

The GRIP-COMPASS trial is a single-center, prospective trial with alternating blocks of patients with blinded evaluation of the primary endpoint. Twelve hundred patients are assigned to the NLP control-target of 4.0 mmol/L or the NHP control-target of 4.5 mmol/L at ICU admission (Figure 1). Allocation to an arm is alternated in blocks of approximately 50 patients until 1200 patients are included, resulting in 24 blocks (Figure 2). Informed consent for inclusion into one of the two study arms was waived by our institutional review board since in both the NLP arm and the NHP arm standard potassium treatment is involved with the only difference that the two therapeutic strategies aim at differing normal levels.

**Figure 1 F1:**
[figure not shown]
**The GRIP-COMPASS flow-chart**. ICU, intensive care unit; GRIP II, glucose and potassium regulation for intensive care patients.

**Figure 2 F2:**
[figure not shown]
**Planned patient allocation scheme**. To create two comparable groups while reducing bias from various time-dependent system effects the GRIP computer is instructed to regularly alternate between the targets of 4.0 and 4.5 mmol/L. The goal is to include 50 patients in each block, where the precise timing of a block change may also depend on logistic factors.

The study will be performed in a 14-bed thoracic-ICU (closed-format) of a tertiary university teaching hospital. The institutional medical ethics committee of the University Medical Center of Groningen approved the study (METc 2009/096). The trial protocol has been registered at ClinicalTrials.gov (NCT 01085071).

### Inclusion

All patients admitted to the thoracic ICU are considered eligible for inclusion. Excluded are those patients who do not have a central venous catheter or an enteral feeding tube because such patients are not entered into the GRIP-II program for potassium regulation since they cannot receive continuous potassium administration to the extent that is regularly necessary. Only rarely will patients be excluded for this reason. Immediately after admission a patient is assigned a potassium control-target that remains unchanged for that patient until discharge to the general ward. The general characteristics of the population admitted to the thoracic ICU are summarized in table 1. The majority of patients (~75%) are admitted after cardiac surgery, i.e. coronary artery bypass surgery (CABG) and/or valve repair.

**Table 1 T1:** General characteristics of expected patient cohort.

	Thoracic ICU
	n = 500
Age (years), median (IQR)	66 (57-74)
Male sex	69%
APACHE II, median (IQR)	14 (10-18)
Reason for admission	
Cardiac surgery	75%
Cardiac arrest	9%
Other surgery	10%
Medical	5%
Miscellaneous	3%
post-operative AFF*	50%
In-hospital mortality	8%

*after cardiac surgery

Baseline characteristics of a recent cohort of 500 patients that were admitted to the thoracic ICU, to provide an impression of the expected patient population in the GRIP-COMPASS trial. The incidence of AFF was observed in a subgroup of 150 consecutive cardiac surgery patients. Abbreviations used in table: ICU intensive care unit; IQR interquartile range; APACHE II acute physiology and chronic health evaluation II score; AFF atrial fibrillation and atrial flutter.

### Potassium regulation

Potassium will be regulated by the computer-assisted decision support system called GRIP-II. This nurse-centered system for both potassium and glucose control was implemented at our ICU in 2004 to improve safety and efficiency. It is, to our knowledge, the first computer-assisted protocol for both glucose and potassium regulation. Both the design and results of both the glucose and potassium algorithm in a large and diverse cohort of ICU patients have been published previously [20-22]. GRIP-II provides a recommendation for the potassium and insulin infusion rate based the patients' potassium and glucose levels and the trend over time. It also gives an advice on the time-interval to the next potassium (and glucose) measurement and monitors if this measurement is performed on time. The average required number of point-of-care measurements per patient per day is 5.6, which is low compared to other computer-assisted glucose protocols [34,35].

Depending on the assigned group (NLP or NHP) GRIP-II will aim for a potassium control-target of 4.0 mmol/L or 4.5 mmol/L. The glucose target ranges are the same for both groups (4.0-7.5 mmol/L). Given the proximity of the targets of the NLP-arm and the NHP-arm that both lie comfortably within the reference range and since the spread in potassium levels actually achieved by GRIP-II was sufficiently small (median 4.3 with an interquartile range of 4.1-4.5 mmol/L) potassium levels for both trial arms are expected to stay within the reference range as well as would be the case without GRIP-II.

Both potassium and glucose are measured in arterial blood samples of 0.5 ml lithium-heparin anticoagulated blood using the ABL-800 series point-of-care analyser (Radiometer Copenhagen, Denmark) that is present on in the ICU. Potassium chloride is administered continuously by syringe pump either parenterally by central venous catheter or enterally. To minimize dosing errors it is administered in a "one-to-one" 1 mmol/ml solution. Potassium chloride suppletion in critically ill patients is efficient and safe in a dose-dependent and predictable way (independent of the use of diuretics or the kidney function) [15,16,36]. The maximum administration rate advised by GRIP-II is 20 mmol/hour. When a higher infusion rate is required, the attending physician can decide to administer more than 20 mmol/hour. Magnesium is supplemented at 30 mmol/day in patients after cardiac surgery [9]. In non-cardiac surgery patients, magnesium is only suppleted when total magnesium levels are <0.80 mmol/L.

### Primary endpoint

The primary endpoint is the incidence of in-hospital atrial fibrillation or atrial flutter (denoted by AFF), confirmed by a 12-lead electrocardiogram (ECG), in patients after cardiac surgery. The reference period over which this primary endpoint is determined is the first 7 days post-surgery, or until hospital discharge if the patient is discharged earlier. The presence of AFF is established by evaluation of all electrocardiograms by independent and qualified cardiologists who are blinded to the treatment allocations.

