### Secondary endpoints

Secondary endpoints include:

- AFF that develops more than 7 days post-surgery and until hospital discharge.

- AFF in patients who do not undergo cardiac surgery during ICU stay, the first week after ICU discharge, until hospital discharge.

- The time course of the incidence of AFF (in cardiac-surgery patients and total patient group).

- The incidence of other serious arrhythmias that require immediate medical intervention (in cardiac-surgery patients and total patient group).

- Time that potassium is in the 3.5-5.0 mmol/L reference range during ICU-admission (in cardiac-surgery patients and total patient group).

- The occurrence of distinct hypokalemia (i.e potassium <2.8 mmol/L) and distinct hyperkalemia (i.e. potassium >6.0 mmol/L) in cardiac-surgery patients and the total patient group, also a safety endpoint.

- Level of glucose control and insulin requirements during ICU admission.

- Biochemical disturbances of electrolytes (sodium, magnesium and calcium), blood gas analysis, lactate and renal function (creatinine, urea) during hospital admission (total patient group).

- Cumulative fluid balance during ICU admission (patients admitted to the ICU for more than 5 days).

- ICU and hospital length of stay (in cardiac-surgery patients and total patient group).

- ICU-mortality and hospital mortality (in cardiac-surgery patients and total patient group, also a safety endpoint) as well as 90-day, and 1 year mortality.

In addition to the cardiac surgery group and the total patient group, the following subgroups will also be compared:

- Patients who underwent CABG with the use of cardiopulmonary bypass versus patients who underwent CABG without cardiopulmonary bypass.

- Patients with a history of AFF prior to surgery versus patients without a history of AFF prior to surgery.

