### Data collection

Baseline patient characteristics are collected at ICU admission (age, sex, length, weight, medical history, medication use, reason of admission). If a patient undergoes (cardiac) surgery, data concerning the procedure and the duration of the procedure (and the time on cardiopulmonary bypass) are collected. For cardiac surgery patients the EuroSCORE model for operative risk stratification is calculated [37]. In non-cardiac surgery patients the APACHE II score is used [38].

This trial requires no specific tests or procedures that are not regularly performed. Daily laboratory tests and blood gas analysis (daily at the ICU, in the general ward only when deemed necessary by the physician) are all part of standard care. During ICU admission all patients are under continuous rhythm monitoring (3-lead) and a 12-lead ECG is done at admission (in cardiac-surgery patients also after 24 and 48 hours), and is repeated when arrhythmias or other complications occur or are suspected. At the general ward a the rhythm is checked regularly and a 12-lead ECG is performed at admission, when deemed necessary by the attending physician, and at discharge. When a patient is prone for severe arrhythmias, continuous monitoring by telemetry is continued at the general ward. All in-hospital ECGs of the included patients are evaluated by the physicians at the ICU and the general ward as well as by independent cardiologists who are blinded for the potassium control-targets.

Potassium and glucose control data (potassium and glucose levels, amount of potassium chloride and insulin administration, number of measurements per day) are automatically stored by the GRIP-II program. All other laboratory tests are stored in the hospital information system. ICU-parameters such as the amount of fluid administered, the use of vasoactive drugs, anti-arrhythmic drugs, diuresis, and the fluid balance are monitored and collected. Minor complications and major complications (e.g. death, stroke, myocardial infarction, organ failure and major bleeding complications) are recorded. Mortality is recorded for the ICU, during hospitalisation and at 90-days. Follow-up information will be obtained from hospital records and the central personal records database.

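### As written, the primary endpoint has no baseline-rhythm condition, so AFF already present on the ICU-admission ECG would count as an event and dilute the comparison; a new-AFF definition is a cheap improvement

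*Protocol article*

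**What the plan says.** The relevant rules stand in four sections of the protocol article.

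- **Primary endpoint.** The endpoint is the incidence of in-hospital AFF confirmed on a 12-lead ECG in patients after cardiac surgery. On the window: "The reference period over which this primary endpoint is determined is the first 7 days post-surgery, or until hospital discharge if the patient is discharged" (that is, before day 7). On ascertainment: "The presence of AFF is established by evaluation of all electrocardiograms by independent and qualified cardiologists", blinded to allocation.
- **Data collection.** During the ICU stay, "a 12-lead ECG is done at admission (in cardiac-surgery patients also after 24 and 48 hours", with repeats when an arrhythmia occurs or is suspected. All in-hospital ECGs go to the blinded cardiologists.
- **Inclusion.** "All patients admitted to the thoracic ICU are considered eligible for inclusion". The only stated exclusion is technical: "Excluded are those patients who do not have a central venous catheter or an enteral feeding tube". On timing: "Immediately after admission a patient is assigned a potassium control-target".
- **Secondary endpoints.** Prior AFF appears only as a planned subgroup: "Patients with a history of AFF prior to surgery versus patients without a history of AFF prior to surgery".

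The Sample size calculation section takes a 50% AFF rate from a pilot of 150 cardiac-surgery patients and plans for a 10% reduction with 400 patients per arm. It also reports that in earlier GRIP-II data patients reached a stable potassium level within 12 hours.

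**The concern.** The window opens at surgery, the admission ECG falls inside it, every ECG is read, and nobody is removed for baseline rhythm. Applied literally, the rule makes a patient who arrives from theatre in AFF an event on the first ECG. The target is assigned only after admission and needs time to act, so that event occurs in either arm whatever the target does.

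Two things are at stake. Such events add about equally to both arms and shrink the risk difference. The result also becomes harder to read, because a null finding could mean no effect on new AFF or an effect diluted by AFF that was already there.

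**Working it through.** **1. The plan's own figure.** Inputs from the Sample size calculation section: p1 = 0.50, p2 = 0.40, two-sided 5%, power 80%, 400 per arm. With a pooled null variance and p̄ the mean of the two rates:

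n = [1.96·√(2p̄(1−p̄)) + 0.8416·√(p1(1−p1) + p2(1−p2))]² / (p1−p2)²

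= [1.96·√0.495 + 0.8416·√0.49]² / 0.01 = (1.379 + 0.589)² / 0.01, which rounds up to 388.

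With a continuity correction it is 408. Both agree with 400. A relative 10% reduction (50% to 45%) would need 1565 per arm, so the plan means 10 percentage points. Power at 400 is Φ[(0.10·√400 − 1.379)/0.70] = Φ(0.887) = 81%; for Fisher's exact test it is 79%. The stated sample size is therefore sound for the rates it assumes.

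**2. Adding AFF present at admission.** Let q be the share of cardiac-surgery patients in AFF on the admission ECG. The documents do not give q, so 5%, 10% and 15% are assumed. Each such patient is an event in both arms.

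- *Scenario A: 50% versus 40% holds in the patients not in AFF, and q comes on top.* p1 = q + 0.5(1−q), p2 = q + 0.4(1−q). Removing the prevalent cases leaves 400(1−q) per arm at 50% versus 40%.
- *Scenario B: the pilot's 50% already contains q, and the planned 20% relative reduction applies to the other events.* p1 = 0.5, p2 = q + 0.8(0.5−q). Removing the prevalent cases leaves 400(1−q) per arm at (0.5−q)/(1−q) versus 0.8 times that rate.

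Example, A at q = 10%: 55% versus 46%. Power = Φ[(0.09·20 − 1.386)/0.704] = Φ(0.588) = 72%.

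| q | Scenario | Rates, all patients | Power, all (400 per arm) | Left per arm | Power, cases removed | Gain (points) |
|---|---|---|---|---|---|---|
| 5% | A | 52.5% v 43.0% | 76.8% | 380 | 79.2% | 2.4 |
| 10% | A | 55.0% v 46.0% | 72.2% | 360 | 77.1% | 4.9 |
| 15% | A | 57.5% v 49.0% | 67.4% | 340 | 74.7% | 7.3 |
| 5% | B | 50.0% v 41.0% | 72.5% | 380 | 75.3% | 2.8 |
| 10% | B | 50.0% v 42.0% | 62.2% | 360 | 68.3% | 6.1 |
| 15% | B | 50.0% v 43.0% | 51.0% | 340 | 60.4% | 9.4 |

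**3. The case with no loss.** If the true difference is 10 points over all cardiac-surgery patients, prevalent cases included, power stays at 81%. The reduction among the other events must then exceed 20%: 10/(50−5) = 22% at q = 5%, 10/(50−10) = 25% at q = 10%, and 10/(50−15) = 29% at q = 15%.

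**The case against.** The strongest objection is that no sentence says AFF on the admission ECG is an event. The sentence on reading all ECGs mainly says who reads them and that they are blinded. Elsewhere the article speaks of incidence, of pilot patients who developed postoperative AFF, and of later AFF that develops, all of which suggests new AFF. This stands in part: that the admission ECG counts is an inference from several sections. A reader might take it as the plan's declared intention, and the documents do not support that. They do fix a window, a set of ECGs and an eligible population, and nothing in those stated rules separates new AFF from AFF already present.

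A reader might also infer that the endpoint definition costs the whole drop from 81% to as little as 51%. It does not. The prevalence is assumed, and removing the prevalent cases recovers only about 2 to 9 points. The rest comes from having fewer patients at risk or from the assumed effect.

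Nor is the comparison shown to be biased toward a false difference. AFF that precedes allocation dilutes toward the null, and an all-patients endpoint is legitimate, only less sensitive.

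Two planned analyses help interpretation: the subgroup by history of AFF and the time course of AFF. Neither changes the primary analysis, and a history subgroup misses AFF that starts between surgery and admission. Conversely, a history of AFF does not make a later event unmodifiable, so excluding on history would go too far. Excluding permanent AF is also unsupported, because the Data collection section lists medical history but not AF type.

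**Conclusion.** The point holds as a weakness in the endpoint definition. Followed literally, the stated rules count AFF present at ICU admission as a primary event, although the target is assigned only afterwards.

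The size depends on two things the documents do not settle: the share of patients in AFF at admission, and whether the planned effect applies to all patients or only to those not yet in AFF. For an assumed 5% to 15%, with the effect confined to the rest, power falls from 81% to between 77% and 67%, or to between 73% and 51% if the pilot rate already includes these cases. If the 10-point difference holds over everyone, nothing is lost. The sample size arithmetic itself is correct. This is a cheap improvement, not an error that must be corrected.

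**What to change.** Define the primary endpoint as AFF first seen on an ECG after the ICU-admission ECG and within the existing 7-day window. Analyse it in cardiac-surgery patients not in AFF on that admission ECG. State that the admission ECG is taken before, or at the start of, potassium control to target; the article gives no order for the ECG and the assignment, and the restriction is free of treatment influence only if this holds. Report AFF present at admission separately by arm, and keep the all-patients version as a sensitivity analysis. Recount the 150-patient pilot under the same rule and restate the power.

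The cost is wording and a recount, since the admission ECG is already routine. The downside is a modestly smaller primary analysis set: 380, 360 or 340 per arm at 5%, 10% or 15%. The change does not by itself restore 80% power. In scenario A that would take 388/(1−q), or 409 to 457 cardiac-surgery patients per arm; in scenario B, 450 to 635. AFF that arises in the first hours, before potassium has settled, would still count.
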